**Secondary Efficacy Endpoints will include:**

- ASAS20 response rate
- Mean change in each of the following domains:
  - VAS patient global assessment
  - VAS pain score
  - Bath AS functional index, BASFI
  - Bath AS global index, BAS-G
  - BASDAI –two morning stiffness-related scores
- Patient global assessment, physician global assessment, nocturnal and total back pain, the BASFI and its independent components, and the BASDAI and its independent components.
- Spinal mobility measured with modified Schober’s test, chest expansion, and occiput-to-wall measurement.
- Patients’ preference scale.
- Quality of life as ASQoL questionnaire.
- Laboratory assessment of inflammation with HS-CRP, Immunoglobulin A and ESR
- Serum creatinine、ALT (SGPT)、CBC

**Safety Evaluation** All patients who receive at least 1 dose of test medicine will be evaluated for safety. The following variables will be assessed: physical examination/vital signs, haematology and chemistry profiles, urinalysis, assessment of extra-spinal and extra-articular involvement, premature withdrawal, adverse events, and serious adverse events during the study.

**Statistical Analysis** Descriptive statistics such as number of observations, mean, median, standard deviation, minimum, maximum and 95% confidence interval will be used to summarize the continuous variables. Frequency and proportion will be used to summarize the categorical variables. The primary analysis will be performed based on the intent-to-treat population. All statistical tests will be two-sided which was evaluated at 5% level significance.

Frequency of dropouts, premature termination of study medication, and withdrawal will be provided and summarized. The last-observation-carried-forward (LOCF) approach will be used to evaluate missing data.

Summary tables for demographic data and baseline characteristics will be provided.

The primary efficacy endpoint is the number of responders as determined by the ASAS Response Criteria for improvement at 20% level at week 8. All patients who withdraw before 8 weeks will be considered non-responders for this endpoint.

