Changes (and percentage changes) from baseline at each visit in the individual components of the ASAS Working Group criteria (VAS patient global assessment, VAS physician global assessment, VAS total and nocturnal pain, BASFI, BASDAI and BAS-G), spinal mobility measures, complete joint assessment, evaluation of hip involvement, and laboratory assessments of inflammation will be analyzed by using paired-t test.

The number and percentage of patients who experience adverse events will be summarized. The number and percentage of patients who experience potentially clinically significant changes in laboratory results, and those who discontinue, will be tabulated. Transition tables from baseline for physical examination and laboratory results will be summarized.

**Rationale for Number of Subjects** Assuming that the BASDAI scores of treatment group (μ1) reduced to 2 from 4, and the BASDAI scores of control group (μ0) reduce to 3.5 from 4. A 2-side test was used, with type Ⅰ error () = 0.05, statistical power (1-) = 0.8 and standard deviation (SD) = 2. The expected dropout rate is 10% in this research. Finally, the study required only 14 subjects in each group to achieve 95% power. The targeted sample size for the study was 30 patients. Therefore, the study had  95% power to detect a treatment effect with this sample size.

**Ethical Considerations** This study will be conducted in accordance with applicable laws and regulations including, but not limited to, the International Conference on Harmonization Guideline for Good Clinical Practice (GCP) and the ethical principles that have their origins in the Declaration of Helsinki. The institutional review board (IRB)/independent ethics committee (IEC) must review and approve the protocol and informed consent form (ICF) before any subjects are enrolled. The subject must be consented using the approved ICF before any procedures specified in the protocol are performed.

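### The claimed 95% power with 14 patients per arm does not follow from the protocol's own inputs, which give about 50%

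*Protocol*

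**What the plan says.** Everything needed is in the Protocol synopsis, mostly under Rationale for Number of Subjects.

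- **Effect.** BASDAI in the treatment group is assumed to be "reduced to 2 from 4", and in the control group to fall from 4 to 3.5.
- **Test.** "A 2-side test was used", with type I error 0.05. The Statistical Analysis section agrees: "All statistical tests will be two-sided which was evaluated at 5% level significance".
- **Power and spread as inputs.** Power is entered as "0.8 and standard deviation (SD) = 2".
- **Dropout.** The inputs continue: "standard deviation (SD) = 2. The expected dropout rate is 10% in this research".
- **Result.** "Finally, the study required only 14 subjects in each group to achieve 95% power". Then "The targeted sample size for the study was 30 patients", and 95% power is claimed for that number as well.

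Study Design says that the 30 patients are randomised equally, so 15 per arm.

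**The concern.** Fourteen per arm is very small for a standardised effect of 0.75, and 95% power at that size is implausible on sight. The paragraph also carries two power values, 0.8 as an input and 95% as the result, and does not show how the 10% dropout enters the number.

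The sample-size statement is what an ethics committee relies on when it approves the trial, and what a reader uses to interpret a non-significant result. With 95% power, such a result would be fair evidence against a 1.5-point benefit of switching. With about 50% power it says little either way.

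**Working it through.** **Inputs (Protocol, Rationale for Number of Subjects, unless noted)**

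- Difference: (4 − 2) − (4 − 3.5) = 2.0 − 0.5 = 1.5
- SD: 2, so d = 1.5/2 = 0.75
- Alpha: 0.05, two-sided
- Number: 14 per arm stated as required; 15 per arm planned (Study Design)
- Dropout: 10%

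**Attempt to reproduce the stated 95%**

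For two independent means with n per arm, the noncentrality is d·√(n/2), referred to a t distribution on 2n − 2 degrees of freedom. At n = 14 this is 0.75 × √7 = 1.98, against a two-sided critical value of 2.06. The expected test statistic lies just below the critical value, so power must be close to one half.

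| n per arm | Power, t test | Power, normal approximation |
|---|---|---|
| 13.5 (27 analysed) | 46.6% | 49.5% |
| 14 | 48.0% | 51.0% |
| 15 | 50.9% | 53.7% |

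The 95% is not reproduced.

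**Number the inputs require**

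By the normal formula, n per arm = 2(z₀.₉₇₅ + z_power)²/d².

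- 80%: 2 × (1.960 + 0.842)²/0.5625 = 27.9, so 28. The t test needs 28.9, so 29. Allowing for dropout, 29/0.9 = 32.2, so 33.
- 95%: 2 × (1.960 + 1.645)²/0.5625 = 46.2, so 47. The t test needs 47.2, so 48. Allowing for dropout, 48/0.9 = 53.3, so 54.

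**Other readings, at 14 per arm (t test) unless noted**

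- One-sided test: 61%.
- The 2 read as a variance (SD 1.41): 77%, or 80% at 15 per arm.
- One-sample test of the adalimumab arm's own 2-point fall, with SD of change 2: 93.2%, or 94.9% at 15.
- ANCOVA on baseline, if SD 2 is the SD of the week-8 score, for assumed baseline/week-8 correlations of 0.5, 0.7 and 0.8: 60%, 76% and 89%. At 15 per arm: 63%, 79% and 91%.
- ANCOVA if SD 2 is instead the SD of change (equal variances at both times; residual SD = 2√((1 + r)/2)), for the same correlations at 15 per arm: 63%, 58% and 55%.

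Only the one-sample test comes near 95%, and it makes no use of the control arm.

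**What would make 95% true**

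At 14 per arm, the SD would have to be about 1.06, or the difference about 2.83. At 15 per arm, the SD would have to be about 1.10, the difference about 2.73, or the ANCOVA correlation about 0.84 with SD 2 as the score SD.

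**Precision at 15 per arm, SD 2**

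The 95% CI half-width is 2.048 × 2 × √(2/15) = 1.50 points, equal to the assumed effect. The difference detectable with 80% power is 2.12 points.

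**Dropout**

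If 14 per arm is the number to be analysed, 14/0.9 = 15.6, so 16 per arm or 32 in all, against 30 planned. If 14 already allows for dropout, 14 × 0.9 = 12.6 per arm would be analysed, with 44% power.

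**The case against.** The arithmetic is not in dispute, and no lost symbol or redaction restores the 95%. The objections concern what surrounds it.

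- **Dropout.** The primary analysis is intention-to-treat with last observation carried forward, so patients who withdraw need not leave the analysis, and 27 analysed is an assumption. The dropout sentence also comes before the 14, which may already include it. Both points stand. Dropout is therefore better described as not shown, and the 32-patient figure is conditional. Neither matters to the conclusion, because power is 47–51% from 27 to all 30 analysed.
- **Test named.** The Statistical Analysis section names a paired t test for changes from baseline, BASDAI included, and a one-sample calculation on the adalimumab arm nearly gives 95%. This may be where the figure came from, though that is inference. It does not validate the claim: the paragraph specifies a mean for each arm and a number for each group, and the trial is a randomised comparison.
- **ANCOVA.** The protocol mentions neither ANCOVA nor a correlation, and does not say whether SD 2 belongs to scores or to change. The phrase about BASDAI scores makes the score SD the natural reading, but the ANCOVA figures remain conditional.
- **0.8 against 95%.** The 0.8 could be a minimum target and 95% the claimed achieved power. That is possible, but neither value is met.
- **Misreading of a null result.** The protocol does not say how a null result would be interpreted, so this is a foreseeable risk and not a stated plan.

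**Conclusion.** The concern holds. On the stated inputs, power for the randomised comparison is 48% at 14 per arm and 51% at 15 per arm, where 95% is claimed. The planned 15 per arm is about half of the 29 that 80% power requires and under a third of the 48 that 95% requires.

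This assumes an unadjusted two-sided 5% t test on BASDAI, a 1.5-point difference and SD 2, all taken or derived from the protocol. The choice between t and normal formulas moves the result by about 3 percentage points. A one-sided test or reading the 2 as a variance still leaves power at or below about 80%. Baseline adjustment would reach 95% only with a correlation of about 0.84 that the protocol does not state.

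The Statistical Analysis section separately names ASAS20 response as the primary endpoint. That conflict needs its own resolution and does not alter this calculation, which is for BASDAI.

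**What to change.** Rewrite the Rationale for Number of Subjects so that one power figure follows from the listed inputs, with the calculation shown.

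- If SD 2 is right, state that 30 randomised patients, a 1.5-point difference and a two-sided 5% t test give about 51% power with all 30 analysed, and about 47% if 10% are lost to analysis. Remove both the 0.8 and the 95%.
- If SD 2 was not the value intended, give the correct SD, say whether it applies to week-8 scores or to change, and recompute.
- State whether the per-arm number is before or after dropout.
- If baseline-adjusted analysis is intended, name it and quote its power only under a stated correlation and a stated meaning of the SD. With SD 2 as the score SD and 15 per arm, this is 63%, 79% or 91% for correlations of 0.5, 0.7 or 0.8.
- Say that the result will be read from the estimated difference and its 95% confidence interval (half-width about 1.5 points), and that a non-significant test will not be taken as evidence of no difference.

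The cost is one rewritten paragraph and a less favourable power statement. The restatement itself needs no extra patients. Holding to 80% or 95% power with these inputs would need 33 or 54 per arm, including 10% dropout.

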# STUDY FLOWCHART

Abbreviations: BASFI = Bath Ankylosing Spondylitis Functional Index; BASDAI = Bath Ankylosing Spondylitis Disease Activity Index. BAS-G = Bath Ankylosing Spondylitis Global Index.

| **Study Procedures** | **Week**  **-4** | **Week**  **0** | **Week 4** | **Week 8** | **Week 12** | **Week 16** |
| --- | --- | --- | --- | --- | --- | --- |
| Visit ID(for sponsor use only) | 1 | 2 | 3 | 4 | 5 | 5 |
| Signed informed consent | X |  |  |  |  |  |
| Medical history | X |  |  |  |  |  |
| Medical history update |  | X |  |  |  |  |
| Inclusion/exclusion criteria | X | X |  |  |  |  |
| Record prior medications | X |  |  |  |  |  |
| Record concomitant medications |  | X | X | X | X | X |
| Physical examination |  |  |  |  |  |  |
| Vital signs |  | X | X | X | X | X |
| Complete joint assessment |  | X | X | X | X | X |
| Patient global assessment |  | X | X | X | X | X |
| Physician global assessment |  | X | X | X | X | X |
| VAS pain score |  | X | X | X | X | X |
| Nocturnal and total back pain |  | X | X | X | X | X |
| BASFI | X | X | X | X | X | X |
| BASDAI | X | X | X | X | X | X |
| BAS-G | X | X | X | X | X | X |
| Modified Schober’s test |  | X | X | X | X | X |
| Chest expansion measurement |  | X | X | X | X | X |
| Occiput-to-wall distance |  | X | X | X | X | X |
| Serum creatinine | X | X |  |  | X | X |
| ALT (SGPT) | X | X |  |  | X | X |
| Erythrocyte sedimentation rate |  | X |  |  | X | X |
| HS-C-Reactive protein |  | X |  |  | X | X |
| Adverse event evaluation |  | X | X | X | X | X |
| Dispense diary cards |  | X | X | X | X | X |
| Dispense test article |  | X | X | X | X | X |
| BP、BW |  | X | X | X | X | X |
| CBC |  | X | X | X | X | X |
| IgA |  | X | X | X | X | X |
| ASQOL |  | X | X | X | X | X |
| finger to floor test |  | X | X | X | X | X |
| L’t lateral bending |  | X | X | X | X | X |
| Shoulder pain or limitation of motion |  | X | X | X | X | X |
| CONCOMITANT MEDICATION |  | X | X | X | X | X |
| ASAS Criteria for response |  |  | X | X | X | X |
| Patients’ preference scale |  |  | X |  |  | X |

The control group: (n = 15)

Etanercept 50 mg sc. weekly

Ankylosing Spondylitis

The treatment group: (n = 15)

Adalimumab 40 mg sc. biweekly

N=30

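### ESR, hs-CRP, ALT and creatinine are not scheduled at weeks 4 or 8, so these four secondary endpoints have no post-baseline value while the arms are on different drugs

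*Protocol*

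**What the plan says.** The Synopsis lists among the secondary efficacy endpoints "Laboratory assessment of inflammation with HS-CRP, Immunoglobulin A and ESR", and on the next line creatinine, ALT and CBC. Under Statistical Analysis, laboratory inflammation is to be analysed by paired t-test as "Changes (and percentage changes) from baseline at each visit". Study Design places evaluations at baseline and at weeks 4, 8, 12 and 16.

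Study Design and Dosage and Administration both keep the control arm on etanercept for the first 8 weeks and move it to adalimumab at week 8. This applies to standard-dose and half-dose patients alike.

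The Study Flowchart is the only place that fixes timing test by test. Its header reads "Study Procedures | Week -4 | Week 0 | Week 4 | Week 8 | Week 12 | Week 16". Under it stand "Erythrocyte sedimentation rate | | X | | | X | X", "HS-C-Reactive protein | | X | | | X | X" and "Serum creatinine | X | X | | | X | X"; the ALT row has the same pattern as creatinine. CBC and IgA are marked at weeks 0, 4, 8, 12 and 16.

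**The concern.** Weeks 0 to 8 are the only period in which one arm is on adalimumab and the other on etanercept. A test that is not done after baseline within that period cannot inform the comparison of the two drugs. It also cannot supply the control arm's value just before its own switch, which is the natural starting point for a switch effect in that arm.

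Two things are at stake. First, the trial is open-label, and BASDAI and most ASAS components are reported by patients who know their drug. ESR and hs-CRP are among the measures least open to expectation. Second, safety is part of the stated objective and chemistry is a named safety variable, yet ALT and creatinine have no scheduled comparison between the drugs. Tests that were never run cannot be recovered by a later analysis plan.

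**Working it through.** The protocol states no figure on this point, so the check is a reading of each flowchart row against its header and a count.

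**Inputs.** Timing of each test: Study Flowchart. Week of the control arm's switch (8): Study Design, and Dosage and Administration. Post-baseline visits up to and including week 8: weeks 4 and 8, so 2.

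**Step 1: count.**

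| Test | Weeks marked | Post-baseline values up to week 8 |
| --- | --- | --- |
| ESR | 0, 12, 16 | 0 of 2 |
| hs-CRP | 0, 12, 16 | 0 of 2 |
| ALT | -4, 0, 12, 16 | 0 of 2 |
| Creatinine | -4, 0, 12, 16 | 0 of 2 |
| IgA | 0, 4, 8, 12, 16 | 2 of 2 |
| CBC | 0, 4, 8, 12, 16 | 2 of 2 |

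The week -4 values of ALT and creatinine are screening values and do not help. IgA shares an endpoint line with hs-CRP and ESR, and CBC shares one with creatinine and ALT, so the schedule splits tests that the endpoint list treats together.

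**Step 2: what weeks 12 and 16 can show.** At week 12 the control arm has had 12 - 8 = 4 weeks of adalimumab, and at week 16 it has had 16 - 8 = 8 weeks. If the treatment arm stays on adalimumab, its exposure is then 12 and 16 weeks. The randomised contrast at those visits is immediate against delayed switching, not adalimumab against etanercept.

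**Step 3: the paired analysis in the control arm.** With Y for a laboratory value and the subscript for the week,

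Y12 - Y0 = (Y8 - Y0) + (Y12 - Y8).

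The first bracket is the change on etanercept and the second the change on adalimumab. Without Y8 only their sum is observed, and the same holds for Y16 - Y0. Reading the sum as a switch effect needs the first bracket to be zero. The protocol does not assume such stability for its clinical score: Rationale for Number of Subjects has the control arm's BASDAI fall from 4 to 3.5, a change of 0.5.

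**Step 4: the missing-data rule.** Last observation carried forward does not fill the gap. Applied to these tests at week 8, it would return Y0, so every patient in both arms would show Y0 - Y0 = 0.

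**Step 5: set against the text.** The planned paired analysis covers every visit, and Study Design names weeks 4 and 8 as evaluation visits. For ESR and hs-CRP the flowchart supplies 2 of the 4 post-baseline visits (weeks 12 and 16), and neither lies in the controlled period.

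**The case against.** The strongest reply is that no promised comparison is lost. The only stated method for laboratory inflammation is a paired t-test, which is within-patient and can be run for ESR and hs-CRP at weeks 12 and 16. No between-arm test of these markers, or of ALT and creatinine, is written down. That is accurate, and the treatment arm's paired change remains usable if that arm stays on adalimumab. It does not rescue the control arm, whose change mixes two drugs, nor does it satisfy the commitment to every visit.

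It may also be said that the text already implies testing at weeks 4 and 8 and that the flowchart is a clerical slip; it does number two visits 5 and lists concomitant medication twice. That may be so, but the flowchart is the only test-by-test schedule, so the two must be reconciled before patients are seen.

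Several stronger readings are tempting, and the protocol does not support them:

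- A reader might infer that no randomised comparison of these tests exists at all. Weeks 12 and 16 still compare the arms as randomised, but on a different question.
- A reader might infer that the main result is damaged. The primary endpoint is named as BASDAI in one place and ASAS20 in another; both are at week 8 and both are scheduled then.
- A reader might infer that the controlled period holds only patient-reported data. IgA, modified Schober's test, chest expansion and occiput-to-wall distance are all taken at weeks 4 and 8.
- A reader might infer that safety cannot be compared between the drugs. CBC, vital signs and adverse events are collected at weeks 4 and 8; the gap is in ALT and creatinine.
- The row "Physical examination" is empty and urinalysis has no row, although both are listed safety variables and the plan says "Transition tables from baseline for physical examination and laboratory results will be summarized". It does not follow that neither will be done. Symbols are lost elsewhere in this text, and an empty row may be such a loss. This is a separate documentation gap and has no bearing on the drug comparison.

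**Conclusion.** The point stands as something that should be fixed, short of a threat to the trial's main conclusion. As scheduled, ESR, hs-CRP, ALT and creatinine have 0 of 2 post-baseline values while the arms are on different drugs, and the control arm has no pre-switch value for any of them. The flowchart contradicts the planned analysis of laboratory inflammation at every visit and the evaluations set for weeks 4 and 8.

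This rests on two assumptions. The first is that the four rows were extracted correctly; each has its full set of cells, the shared blanks at weeks 4 and 8 look deliberate, and neighbouring rows read normally. The second is that the treatment arm remains on adalimumab after week 8, which the protocol does not say in words. If it does not, weeks 12 and 16 compare something else again, but still not the two drugs, because no control patient is planned to be on etanercept then.

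**What to change.** Amend the flowchart to mark ESR and hs-CRP at week 8, ideally also at week 4, and do the same for ALT and creatinine so that these laboratory results can be compared between the drugs. State that the control arm's week-8 sample precedes its first adalimumab dose, and name week 8 as the between-arm time point for these endpoints. Align the analysis text with the amended schedule.

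For all four tests in 30 patients, week 8 alone adds 4 x 30 = 120 results, and weeks 4 and 8 together add 240. No visit is added, and blood is already drawn at both visits for CBC and IgA. An extra tube may be needed, because the protocol gives no sample types or volumes.

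The alternative is to move the week-12 ESR and hs-CRP to week 8. The number of ESR and hs-CRP assays then stays the same (2 x 30 = 60 moved), at the price of the week-12 values.

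Separately, reconcile the empty physical-examination row and the absent urinalysis row with the listed safety variables and the promised transition tables. How often these are done, and how often chemistry is needed for patient monitoring, is a clinical decision for the sponsor and the investigator.
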